## Abstract

**Background:**

Post-craniotomy pain is a common occurrence which is associated with poor outcomes. Pre-emptive scalp infiltration with dexamethasone and ropivacaine has been proven effective in previous studies but with limited clinical significance. Dexamethasone palmitate emulsion (D-PAL) is a pro-drug incorporating dexamethasone into lipid microspheres with greater anti-inflammatory activity and fewer side effects than free dexamethasone. However, its effects in post-craniotomy pain management remain unknown. This study hypothesizes that pre-emptive scalp infiltration with ropivacaine plus D-PAL emulsion can achieve superior analgesic effects to ropivacaine alone in adult patients undergoing craniotomy.

**Methods/design:**

This is a single center, randomized controlled trial enrolling 130 patients scheduled for supratentorial craniotomy, which is expected to last longer than 4 h. We compare the efficacy and safety for postoperative pain relief of ropivacaine plus D-PAL group and ropivacaine alone group following pre-emptive scalp infiltration. Primary outcome will be pain Numerical Rating Scale at 24 h postoperatively. Secondary outcomes will include further analgesia evaluations and drug-related complications within a follow-up period of 3 months.

**Discussion:**

This is the first randomized controlled trial aiming to assess the possible benefits or disadvantages of D-PAL emulsion for incisional pain in craniotomy. It may provide an alternative to optimize pain outcome for neurosurgical patients.

**Trial registration:**

ClinicalTrials.gov (NCT04488315). Registered on 19 July 2020.

**Supplementary Information:**

The online version contains supplementary material available at 10.1186/s13063-022-06936-z.

## Background

Over two-thirds of patients have been reported to suffer moderate to excruciating incisional pain during the first 48 h after neurosurgical craniotomy [1, 2]. Inadequate pain control can predispose one to elevated intracranial pressure, leading to devastating neurological complications such as cerebral hyperemia, edema, and hemorrhage. Moreover, acute severe pain can subsequently develop into chronic pain and headache affecting up to 30% of patients, which are attributed to an increased risk of peripheral and central sensitization by the sustained noxious input [3, 4]. All these provide impetus to define the ideal options for pain management to improve postoperative care for patients undergoing craniotomy.

However, there are no guidelines for post-craniotomy pain management yet. Traditionally, systemic opioids are the mainstay of treatment. However, therapeutic doses of opioids are associated with a moderate-to-high risk of postoperative nausea and vomiting (PONV). And the postoperative neurological assessments would be delayed or interfered due to sedation and miosis caused by opioids. Also, opioid-induced respiratory depression could lead to hypoxia and hypercarbia, which subsequently increase cerebral blood flow and intracranial pressure [5]. So opioids are often used sparingly for fear of adverse effects. Other systemic analgesic drugs, for example, nonsteroidal anti-inflammatory drugs (NSAIDs), gabapentin, and ketamine, appear to be effective, but none are considered adequate to alleviate pain without risks for neurological recovery [6]. Furthermore, systemic administration is usually used after the occurrence of pain when the peripheral and central sensitizations have already developed, leading to less pronounced analgesic effects [7]. Hence, it is important to explore multimodal analgesia to provide better pain control and to minimize the reliance on systemic analgesics [8].

At present, the benefits of regional anesthesia have been positively valued, which indicate more effective and stable effects than intravenous analgesia within 24 h postoperatively [9]. Wound infiltration with local anesthetics (LAs) is the simplest, safest, and most effective regional anesthesia to prevent incisional pain in craniotomy [10]. Preemptive scalp infiltration with long-acting local anesthetics such as ropivacaine has been reported to ensure a reduced perioperative consumption of opiates and a delayed need for rescue analgesic after craniotomy [11]. However, the efficiency only lasts for a relatively short period after a long perioperative duration of craniotomy which usually exceeds 4-6 h [12]. Furthermore, previous studies have provided unsatisfactory or conflicting data in attempts to prolong the block of pain conduction by adding epinephrine or using lipid microspheres or liposome formula of local anesthetics [11, 13, 14]. Thus, the induction of sufficient and prolonged analgesic efficacy after craniotomy still remains a big challenge to clinicians.

It has been reported that post-craniotomy pain originates from the damage of muscles and soft tissues at surgical site. It is caused by the release of inflammatory mediators after incisional injury, which activate the peripheral nociceptors and lead to abnormal action potential transmitted along afferent Aδ and C-fibers [15, 16]. Therefore, drugs with a powerful local anti-inflammatory property, such as glucocorticoids, might play a pivotal role in preventing or reducing postoperative pain [17, 18]. Our research group has previously demonstrated that the addition of Diprospan (a combination of betamethasone sodium phosphate and betamethasone dipropionate) to local anesthetic ropivacaine (0.5%) successfully reduces post-craniotomy pain with an 87% decrease in opioids consumption in a follow-up of 48 h [19]. However, a recent laboratory research cautioned that the mixing of ropivacaine with betamethasone sodium phosphate could produce obviously larger crystals (> 50 μm) than with dexamethasone sodium phosphate (< 10 μm) [20]. Therefore, dexamethasone is preferred for injection in consideration of effectiveness and safety. Pre-emptive scalp infiltration with the addition of dexamethasone sodium phosphate to 0.5% ropivacaine has ensured a significant decrease in opioids consumption and pain scores within postoperative 72 h, which is consistent with physiological effects of dexamethasone with a longer half-life of 36-72 h [6, 21]. However, the positive results might have limited clinical significance concerning the absolute differences compared to the control group, which have also been observed in pediatric patients [6, 22].

Dexamethasone palmitate emulsion (D-PAL emulsion) is a pro-drug incorporating dexamethasone palmitate (D-PAL) into lipid microspheres. It is gradually hydrolyzed to dexamethasone by carboxylesterase in the reticuloendothelial system and some inflammatory cells but not in human serum, therefore indicating an uptake of 8 times higher and an anti-inflammatory activity of 5-6 times greater than its corresponding amount of free dexamethasone. Furthermore, the location of D-PAL at inflammatory lesions could reduce the risks of systemic side effects [23, 24]. The efficacy of D-PAL has been verified in multiple disorders including rheumatoid arthritis, systemic lupus erythematosus, macrophage activation syndrome, arteriosclerosis, and asthma [24–27]. For pain management, intra-articular infiltration of D-PAL in combination with mepivacaine is considered to be a safe and effective method for acute lumbar facet syndrome with no side effects [28]. Epidural injection of D-PAL has relieved edema and pain more effectively when applied after intradiscal electrothermal (IDET) treatment for discogenic pain [29]. To the best of our knowledge, no studies have evaluated the addition of D-PAL to local infiltration analgesia for neurosurgical patients. Here, we hypothesize that pre-emptive scalp infiltration with ropivacaine plus D-PAL emulsion can achieve superior analgesic effects to ropivacaine alone in adult patients undergoing craniotomy, so as to provide a clinical option of pre-emptive analgesia for post-craniotomy pain.

## Study design and methods

### Study design

This trial is a prospective, single-center, randomized, open-label, and blinded-endpoint study. Participants will be assigned to either ropivacaine plus D-PAL group or the ropivacaine alone group in an allocation ratio of 1:1 for this superiority trial. The trial will be conducted at Beijing Tiantan Hospital, Capital Medical University, China, from October 2022. We have used the SPIRIT reporting guidelines [30] and completed SPIRIT checklist (Supplementary file 1) and SPIRIT figure (Fig. 1). The flow diagram is illustrated in Fig. 2.

**Fig. 1 Fig1:**
[figure not shown]
The schedule of enrollment, allocation and assessments. Abbreviations: D-PAL, dexamethasone palmitate emulsion; PCA, patient-controlled analgesia; NRS, numerical rating scale; OC/APAP, oxycodone /acetaminophen; Dex, dexamethasone; PONV, postoperative nausea and vomiting; WHOQOL-BREF, World Health Organization QoL abbreviated version; POSAS, Patient and Observer Scar Assessment Scale; hr, hour; mon, month; iv, intravenous

**Fig. 2 Fig2:**
[figure not shown]
CONSORT flow diagram of the trial

### Objectives

The primary objective of this trial is to determine whether preemptive incisional infiltration with ropivacaine plus D-PAL is superior to ropivacaine alone in relieving postoperative pain for adults undergoing neurosurgical craniotomy. The effects of both interventions on postoperative pain management and patients’ safety and quality of recovery will also be compared.

### Recruitment and ethics

The study plan is in accordance with “Declaration of Helsinki” and approved by the Ethics Committee of Beijing Tiantan Hospital (KY-2018-034-02-8). The strategy has been registered at ClinicalTrials.Gov (NCT04488315, Principal investigator: [name], Date of registration: July 19, 2020). This trial does not involve biological specimens, and protocol modifications will be not expected. All patients scheduled for elective supratentorial craniotomy for resection of a tumor, clipping of an unruptured aneurysm, or removal of an epileptic focus will be recruited and screened for participation by one researcher. This independent research will also be responsible for obtaining the informed consent by visiting the eligible patients 1 day before surgery and providing them with a verbal explanation of the written consent. Each participant will have sufficient time to ask any questions or concerns regarding this study and then decide whether to participate in this study. Eligible patients will sign informed consent and participants will have the right to withdraw their consent or discontinue participation without restrictions at any time point throughout the study. The confidentiality of participant data will be protected and patients will have the right to obtain relevant information and decide whether their data is to be shared with the regulatory authorities on reasonable request.

### Eligibility criteria

#### Inclusion criteria

Scheduled for elective supratentorial craniotomy with an anticipated duration of > 4 hAmerican Society of Anesthesiologists (ASA) physical status of I-–IIAge 18-64 yearsAnticipated tracheal extubation, full recovery, and cooperation within 2 h postoperatively

#### Exclusion criteria

Preoperative Glasgow Coma Scale < 15History of craniotomyUnable to comprehend the pain Numerical Rating Scale (NRS)Extreme body mass index (BMI) of < 15 or > 35Peri-incisional infectionAllergy to dexamethasone, ropivacaine, or other analgesicsHistory of alcohol or drugs abuse (more than 2 weeks)History of psychiatric disorders, uncontrolled epilepsy, or chronic headacheHistory of severe cardiopulmonary, renal, or liver dysfunctionHistory of radiation therapy and chemotherapy or with a high probability of such treatment postoperativelyPregnant or breastfeedingRefusal to give written informed consent

#### Withdrawal criteria

Operation duration ≤ 4 hNot awake or extubated within 2 h after surgeryUnexpected radiation therapy or chemotherapy postoperativelyRevision for hematoma or brain swelling except wound problems within 72 h after surgeryGCS < 15 within 72 h after surgeryPoor cognitive function within 72 h after surgeryHaving a fever (≥ 39°C) within 72 h after surgeryLost in follow-upVoluntary withdrawal

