### Pre-incisional infiltration

Patients will receive pre-emptive infiltration by the neurosurgeon immediately before head fixation in a sterile fashion. A 22-gauge needle will be introduced into the planned incision site, as well as each pin fixation site of the Mayfield head holder, at a 45° angle and throughout the entire thickness of the scalp. The ropivacaine plus D-PAL group will receive 0.027% D-PAL and 0.5% ropivacaine, whereas the ropivacaine alone group will be injected with 0.5% ropivacaine alone. The total volume of the local infiltrated solution will be at the discretion of the neurosurgeon, based on the length of the incision.

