### Additional interventions

Patients will be evaluated to check fitness for NRS assessment 1 h after shifting to PACU, using a modified questionnaire of the Short Orientation Memory Concentration (SOMC) test [32]. The cognitive function of patients will be rated as good, able to recall and count with minimal mistakes (1-3); fair, with ≥ 3 mistakes; and poor, not able to recall at all. For patients regarded as poor, the same test will be repeated 1 h later. If the grading is poor again, then that patient will be withdrawn from the study [33]. A  PCA device containing sufentanil 200 μg and ondansetron 16 mg in 100 mL saline will be set up to deliver 1 mL as an intravenous bolus with a 10-min lockout interval after craniotomy. The maximum dose will be limited to 8 μg per hour, and there will be no initial dose or background infusion. Patients will be advised to push the analgesic demand button if they feel pain and to repeat it until the pain is relieved. PCA regimen will be discontinued when it is no longer needed. Each press will be recorded by an electronic memory system, including both valid and invalid presses. Patients will be given an oral supplementary tablet of oxycodone (OC)/acetaminophen (APAP) 5/325 mg (Mallinckrodt Inc., USA) for rescue analgesia when NRS score > 4 after receiving four times of bolus with the PCA device. OC/APAP will be prescribed at an interval of at least 6 h until the end of our study. Total doses of rescue analgesia consumed will be recorded.

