#### Secondary outcome

Pain NRS scores at 2, 4, 12, 48, and 72 h after craniotomy;

Prolonged post-craniotomy pain NRS at 1 and 3 months;

Number of patients needing no sufentanil at 24, 48, and 72 h after craniotomy;

Total consumption of sufentanil with PCA device at 24, 48, and 72 h postoperatively;

Total number of times that patients press the PCA button, including valid and invalid presses at 24, 48, and 72 h postoperatively;

Time to first PCA button press after surgery;

Time to first rescue analgesia with OC/APAP after surgery;

Duration of hospitalization postoperatively.

PONV scores at 24, 48, and 72 h after surgery. PONV is rated by patients as 0, absent; 1, nausea not requiring treatment; 2, nausea requiring treatment; and 3, vomiting.

WHOQOL-BREF scores at 1 and 3 months after craniotomy. The WHOQOL-BREF is a questionnaire of 26 items, including social relationships (3 items), physical health (7 items), psychological health (6 items), environment (8 items), overall QoL (1 item), and general health (1 item). Each domain’s mean score can range between 4 and 20 with a higher score indicating a better QoL.

Local soft-tissue atrophy at 72 h, 1 and 3 months after craniotomy. It is presented as superficial atrophy of skin and adipose tissue, central discoloration of the skin, yellow subcutaneous deposits, small sebaceous glands, cessation of hair growth, or mauve colored periphery at the injection site.

Wound healing score at 72 h, 1 and 3 months postoperatively. Wound Healing Score is rated by an independent researcher as excellent, good, and suboptimal.

Patient and Observer Scar Assessment Scale (POSAS) at 72 h, 1 and 3 months after craniotomy [35]. POSAS consists of 2 numerical numeric scales, the observer component, and the patient component.

Other complications such as respiratory depression, allergic reaction, local or systemic toxicity, wound infection, hematoma, and injection site infection throughout the treatment and follow-up period.

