### Safety assessment

In this study, adverse events (AEs), defined as negative or unintended clinical manifestations throughout the treatment and follow-up period, will be monitored and recorded in detail on a case report form (CRF). All AEs related to the surgery, anesthesia, steroid, or analgesics, together with the soft-tissue atrophy and local infection, which might be induced by scalp infiltration with the mixture of ropivacaine and D-PAL emulsion, should be monitored during the 3 months’ follow-up. The soft-tissue atrophy, clinically manifested as superficial atrophy of skin and adipose tissue, central discoloration of the skin, yellow subcutaneous deposits, small sebaceous glands, cessation of hair growth, or mauve-colored periphery at the site of injection [36], will be monitored by careful observation and will be evaluated partly by the Patient and Observer Scar Assessment Scale (POSAS) and Wound healing score at 72 h, 1 m, and 3 months after craniotomy. AEs will be treated and reported to the Institutional Review Board (IRB) as soon as possible. Study interventions-related AEs will be treated for free. The trial will be terminated immediately in case of serious life-threatening AEs leading to prolonged hospital stay or death.

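### Treated patients are withdrawn for events that follow randomisation, and the 3-month-completer rule then removes them from analyses described as intention-to-treat

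*Protocol article*

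**What the plan says.** Timing (Protocol article, Pre-incisional infiltration): "Patients will receive pre-emptive infiltration by the neurosurgeon immediately before head fixation in a sterile fashion". Every later event therefore comes after study treatment.

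Withdrawal criteria: apart from voluntary withdrawal and loss to follow-up, the list contains an operation of 4 h or less, not being awake or extubated within 2 h, unexpected radiotherapy or chemotherapy (no time limit given), revision "for hematoma or brain swelling except wound problems within 72 h after" surgery, GCS below 15 or poor cognition within 72 h, and "a fever (≥ 39°C) within 72 h after" surgery. Additional interventions repeats the cognition rule for a second failed test: "If the grading is poor again, then that patient will be withdrawn from the study".

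Outcomes: Secondary outcome lists, among other complications, "wound infection, hematoma, and injection site infection throughout the treatment and follow-up period". Safety assessment defines adverse events broadly, as "defined as negative or unintended clinical manifestations throughout the treatment and follow-up period", with 3 months of monitoring.

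Handling of these patients:
- Statistics limits all analyses to patients who complete 3 months and in the same sentence invokes intention-to-treat. It compares adverse events in a safety data set that the article does not define.
- Data collection and management keeps the data of patients who discontinue or deviate up to the point of termination, unless they could not give the 24 h primary outcome.
- Missing data states that multiple imputation will be used for the whole study.

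**The concern.** Withdrawal here is not limited to patients who no longer wish to take part. It takes treated patients out because of what happened to them after treatment, and two comparisons are at stake.

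**Safety.** A hematoma needing revision is a complication that the trial means to count, and it is also a reason to leave. Once withdrawn, the patient cannot complete 3 months. Read literally, the Statistics section then excludes the patient, and the 1- and 3-month wound, scar and atrophy assessments are not made. The Discussion concedes that the trial is too small to identify rare harms, so each lost case matters.

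**Pain.** Some triggers may depend on arm by the protocol's own reasoning. Background says that poor pain control can lead to edema and hemorrhage, and that postoperative "neurological assessments would be delayed or interfered due to sedation and miosis caused by opioids". If one arm has better analgesia and uses less sufentanil, the rates of revision, GCS below 15 and poor cognition could differ. Comparing only those who remain then no longer compares the randomised groups. The 20% dropout allowance restores numbers, not comparability.

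**Working it through.** **1. The plan's own figure.** Inputs from Sample size: 2.0 ± 1.5 v 1.2 ± 0.9, alpha 0.05, power 90%, dropout 20%. Statistics gives two-tailed tests and Study design gives 1:1 allocation.
- Target difference = 2.0 − 1.2 = 0.8.
- Root-mean-square SD = √((1.5² + 0.9²)/2) = √1.53 = 1.237.
- The normal approximation gives 51 per arm. The unequal-variance t test gives 52 (power 0.903).
- 52/(1 − 0.20) = 65 per arm, total 130. The figure reproduces and is not in dispute.
- The allowance is 0.20 × 130 = 26 patients, 13 per arm.

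**2. What the text does to a withdrawn patient.**

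| Patient | Data collection and management | Missing data | Statistics |
|---|---|---|---|
| Withdrawn before the 24 h score | data not kept | imputed | excluded (not a 3-month completer) |
| Withdrawn at 24-72 h, 24 h score given | kept to exit | later values imputed | excluded |
| Later radiotherapy or chemotherapy, 24 h score given | kept to exit | later values imputed | excluded |

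No row is consistent. Retention and imputation cannot help a patient whom the completer rule has already taken out. In the first row the retention rule itself drops the patient.

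**3. Possible effect on the pain difference.** The documents give no withdrawal rates and no scores for withdrawn patients, so everything here is assumed. Let a fraction p be withdrawn, with mean score e points above those retained in the same arm. Then

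all-randomised mean = retained mean + p × e.

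The shift in the between-arm difference is (p₁ − p₂) × e. With 20% v 10%:
- e = 1: 0.10 × 1 = 0.10 points; 0.10/0.8 = 12.5%, about 13% of the target.
- e = 2: 0.10 × 2 = 0.20 points; 0.20/0.8 = 25%.

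This means 13 + 6.5 = 19.5 withdrawals, inside the allowance of 26.

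**4. Same rates, with the excess measured from the overall mean.** The retained mean is then lower than the overall mean by p × e/(1 − p). The shift per point is 0.20/0.80 − 0.10/0.90 = 0.139. Assume no true effect, SD 1.5 in both arms and 65 randomised per arm. About 52 and 58.5 remain, and the standard error is 1.5 × √(1/52 + 1/58.5) = 0.286.

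| Excess above overall mean | Spurious difference | Chance of P < 0.05 |
|---|---|---|
| 1 | 0.14 | 7.7% |
| 2 | 0.28 | 16.3% |
| 3 | 0.42 | 30.8% |

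**5. Limits of the illustration.** With equal withdrawal (10%/10% or 20%/20%) and equal excess, the shift is 0 and the rejection rate is 5%. Swapping the arms reverses the sign.

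**The case against.** The strongest reply is that the article already protects these patients. Data are kept up to exit, multiple imputation is promised, and a separate safety data set is named that a fuller plan may define. A hematoma revision at 30 h in a patient with a 24 h score would then be counted. That is a fair reading of those sections taken alone. It does not survive the completer rule, which covers all analyses, and it gives nothing to patients withdrawn before 24 h. An undefined safety set could be left to another document; a stated rule that contradicts it cannot.

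Second, some criteria have a purpose. A pain score from a patient with low GCS or failed cognition may be invalid, and an operation of 4 h or less falls outside the target population. The first point justifies a missing score, not removal of the patient. On the second, no route from infiltration to operation length is evident, so the likely cost is precision rather than bias. Waking and the PACU cognition tests also come so early that PCA use has had little time to differ.

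Third, the hematoma listed as a complication stands between two wound-related items and may not be the intracranial event that prompts revision. The wording leaves this open, but the adverse event definition is broad enough to cover either.

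A reader might go further, in ways that the documents do not support:
- That infection triggers withdrawal. No criterion names infection, and wound problems are expressly exempt from the revision criterion.
- That unblinded surgeons apply the triggers. The neurosurgeons know the allocation, but nothing says who applies the criteria, and follow-up belongs to blinded researchers.
- That the steroid changes the fever criterion. The documents give no such link.
- That the pain result is shown to be biased in a known direction. If the control arm lost more high-pain patients, the bias would run against D-PAL. Patients withdrawn for sedation need not have more pain at all.

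**Conclusion.** The point holds in this form: treated patients are withdrawn for post-randomisation events, and the sections on retention, imputation and analysis population contradict one another about them. If the completer rule governs, the analysis is not intention-to-treat.

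For safety, the loss follows from the text as written and needs no assumed rates: hematoma-revision cases and their later follow-up can drop out. How many cannot be known from the article.

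For pain, bias is possible but not demonstrated. It requires withdrawal rates, or the kind of patient withdrawn, to differ by arm. The shift of 0.10 to 0.20 points rests wholly on the assumed 20% v 10% split and the assumed 1 to 2 point excess over retained patients.

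**What to change.** Reconcile Withdrawal criteria, Additional interventions, Data collection and management, Missing data and Statistics, so that one rule governs:

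1. Reserve withdrawal for consent withdrawn, and report loss to follow-up as such. Record the other listed events as post-randomisation events and continue follow-up to 3 months.
2. Replace the 3-month-completer restriction with all randomised patients, analysed in their allocated arm. Delete the exception for patients without a 24 h score.
3. Set an NRS score to missing, and impute it, only where the patient cannot give one.
4. Define the safety data set as every patient who received any infiltration, with all adverse events counted, including hematoma that leads to revision.
5. Report the number of patients with each event by arm.
6. Keep the present exclusions as a per-protocol sensitivity analysis.

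The cost is protocol wording and follow-up of patients who would otherwise have left. Some noisier NRS values will enter the primary analysis. Trial status says that recruitment has not begun, so the change can be made before any patient is affected.
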